# Exploratory, multicenter, open-label study to evaluate the effects of linaclotide in patients with chronic constipation with an insufficient response to magnesium oxide: A study protocol

**DOI:** 10.1016/j.conctc.2022.101019

**Published:** 2022-10-28

**Keywords:** Chronic constipation, IBS-C, Magnesium oxide, Linaclotide, JPAC-QOL

## Abstract

**Background:**

Chronic constipation leads to poor quality of life, and treatment remains unsatisfactory for patients. In Japan, magnesium oxide has been commonly used as the first choice of treatment for constipation; however, there are some cases of low satisfaction with magnesium oxide treatment. Linaclotide has recently been used to treat chronic constipation. In this study, we will examine whether linaclotide improves symptoms and quality of life in patients showing insufficient response to magnesium oxide.

**Methods:**

This is an exploratory multicenter open-label study. The target number of patients is 64: 32 patients with and 32 without abdominal symptoms. Patients with chronic idiopathic constipation or irritate bowel syndrome with constipation diagnosed according to the Rome-IV criteria are eligible. Patients prescribed 0.99–2 g/day of magnesium oxide for at least 4 weeks will be included. Those who consent to the study will continue taking magnesium oxide for 2–4 weeks, and defecation will be documented. Patients who meet the criteria will be prescribed linaclotide (0.5 mg) daily for 12 weeks. The primary endpoint is a change in the Japanese version of the Patient Assessment of Constipation Quality of Life (JPAC-QOL) score after 12 weeks of treatment.

**Conclusion:**

This is the first study to investigate the usefulness of linaclotide as a second-line treatment for chronic constipation. We will test the efficacy of treatment of constipation in patients with inadequate response to magnesium oxide.

**Trial registration:**

This study is registered with the Japan Registry of Clinical Trials (jRCT, jRCTs031200048).

## Introduction

1

The prevalence of chronic constipation in adults is estimated at an approximate 15%, and its incidence increases with age [1,2]. Patients with irritable bowel syndrome (IBS) show no organic abnormalities in the small or large intestine, although abnormal bowel movements and uncomfortable abdominal symptoms persist. IBS with constipation (IBS–C) presents with chronic constipation accompanied by abdominal pain and discomfort and is referred to as chronic constipation along with chronic idiopathic constipation (CIC). Patients with chronic constipation have decreased quality of life and low treatment satisfaction [3,4]. Therefore, appropriate medical treatment is required for patients whose quality of life remains impaired by treatment.

In Japan, magnesium oxide (MgO) has long been used to treat chronic constipation. It is classified as an osmotic laxative that facilitates defecation by promoting water secretion in the intestinal lumen and softens the stool. With as many as 10 million prescription users, MgO is widely prescribed in Japan because it is inexpensive, and its dosage can be adjusted by the patients themselves. However, some patients, especially those with renal dysfunction and the elderly, develop hypermagnesemia after taking MgO, which is why it is recommended that their serum magnesium levels be periodically measured [5]. Therefore, prescribing MgO to these patients requires special attention.

Linaclotide is a 14-amino acid peptide guanylate cyclase-C (GC-C) receptor agonist that increases cyclic guanosine monophosphate (cGMP) levels in the intestinal epithelial cells and causes chloride secretion into the lumen, thereby promoting water secretion and bowel movements. It also improves intestinal hypersensitivity, thereby relieving abdominal pain and discomfort [6]. Linaclotide was approved by the Japanese Ministry of Health, Labour, and Welfare in 2016 for use in patients with IBS-C, with an additional indication for chronic constipation in 2018. Linaclotide can be used as a secondary treatment for chronic constipation. Although many patients in Japan take MgO, cases of ineffectiveness have been observed. Clinical trials that evaluated the efficacy of linaclotide as a first-line treatment, such as those reported by Lembo et al. [7], have been conducted previously; however, cases of inadequate response to conventional laxatives have not been reported. Herein, we describe the protocol for our study on the efficacy and safety of switching to linaclotide as a secondary treatment for 12 weeks in patients who show an inadequate response to primary treatment with MgO.

## Methods

2

### Trial design

2.1

This is a multicenter, open-label, exploratory study to evaluate the efficacy of linaclotide in patients diagnosed with CIC or IBS-C and inadequately responding to MgO. The study will be conducted at Yokohama City University Hospital, Kanagawa Dental University Yokohama Clinic, and Namiki Koiso Medical Clinic. The study will be managed by the YCU Center for Novel and Exploratory Clinical Trials (Y-NEXT); the administrative office is located at Yokohama City University. Data will be entered and collected by an electronic data capture (EDC) system.

### Ethical considerations and trial registration

2.2

This study will be conducted in accordance with the principles of the Declaration of Helsinki and approved by the Ethics Committee of Yokohama City University on April 24, 2020 (CRB19-013); it was registered in the Japan Registry of Clinical Trials (jRCT) on June 9, 2020 (jRCTs031200048). All the patients will provide written informed consent. The results obtained from this study will be promptly published through conference presentations or journal article submissions. When publishing the results, necessary measures will be taken to protect the human rights of the research subjects and others involved or the rights and interests of the researchers and others involved.

### Drug supply

2.3

Linaclotide provided by Astellas Pharma Inc. will be used in this study. The principal investigator at each site and study medication manager will store and manage the study medication in accordance with the study medication management protocol. The subjects will be instructed to take linaclotide (0.5 mg) once daily. Medication adherence will be monitored using a patient diary and any remaining medication that the patients bring with them.

### Sample size estimation

2.4

The target number of cases in the study is 64. Of these, 32 subjects with abdominal symptoms and 32 without abdominal symptoms will be recruited. This is an exploratory study owing to the lack of data on the Japanese version of the Patient Assessment of Constipation Quality of Life questionnaire (JPAC-QOL) with linaclotide administration. In addition to the primary objective of evaluating the drug response in the overall population, the secondary objective is to evaluate the effectiveness in subgroups based on abdominal symptoms (with and without). The number of patients in each subgroup will be set to ensure 90% statistical power when a paired *t*-test is used at a two-sided significance level of 5% for assessing the change in the JPAC-QOL total score between the baseline and 12 weeks after treatment. A 90% power for each subpopulation will ensure that the main analysis, or the analysis for the total population, has a power of 90% or more if the effect size assumed for each subpopulation is correct. A long-term study of elobixibat in patients with chronic constipation showed that the mean age was 43.9 years and the mean change (standard deviation) in the JPAC-QOL overall score from baseline to week 12 was −0.69 (0.68) [8]. We will consider equivalent or better efficacy of a long-term study of elobixibat as clinically meaningful and set a target number of patients. Miller et al. reported that age is inversely correlated with baseline JPAC-QOL total scores [9]. Considering that the average age of the patients in this study is expected to be approximately 60 years, and assuming a 33% decrease in the mean change in the JPAC-QOL responses and no changes in the standard deviation, the mean change in the JPAC-QOL overall score from baseline to week 12 was assumed as −0.46 (0.68). Under this assumption, 25 subjects would be needed in each subpopulation to detect a significant change from baseline in the JPAC-QOL total score at week 12, with a power of 90% or greater. Assuming a 20% dropout rate during the study period, the target number of patients in each subpopulation in this study is 32. Therefore, the overall target number of cases is calculated as 64.

### Eligibility criteria

2.5

Patients with CIC and IBS-C will be evaluated according to the Rome-IV criteria [10]. The principal investigator or sub-investigator will check the inclusion and exclusion criteria listed in Table 1 and determine whether the patients meeting the inclusion criteria are eligible. Patients enrolled at this point will be checked at visit 2 to determine whether they meet the medication initiation criteria. Patients who do not meet the medication initiation criteria will be excluded from the study. If they meet the medication initiation criteria, linaclotide prescription will be started.

**Table 1 tbl1:** Criteria for inclusion, medication initiation, and exclusion.

**Eligibility criteria**	
**Inclusion criteria**	**Exclusion criteria**
1. Written consent is obtained from the patient.	1. Patients with a history of surgical resection of the stomach, gall bladder, small intestine, or colon. However, appendicitis and benign polypectomy are excluded.
2. Patients diagnosed with CIC or IBS-C based on Rome-IV criteria and prescribed MgO 0.99 g–2 g per day for at least 4 weeks.	2. Patients with a history of or currently suffering from inflammatory bowel disease such as Crohn's disease or ulcerative colitis
3. Outpatients whose age at the time of obtaining consent is 20 years or more but less than 85 years.	3. Patients with a history of or currently suffering from ischemic colitis.
4. Patients who are not likely to become pregnant or who agree not to become pregnant until 4 weeks after the last dose of linaclotide.	4. Patients currently suffering from infectious enteritis.
	5. Patients currently suffering from hyperthyroidism or hypothyroidism.
	6. Patients with obvious mechanical obstruction (bowel obstruction due to hernia, etc.).
**Medication initiation criteria**	7. Patients with megacolon or megarectum.
1. Patients with a mean JPAC-QOL total score of 1.0–2.5 at the beginning of the treatment.	8. Patients currently suffering from constipation due to recto-anal dysfunction.
2. Patients who complete all items in the patient diary during the pre-observation period for at least 10 days (at least 5 days per week) during the 14 days prior to the start of treatment.	9. Patients currently suffering from medication-induced constipation.
3. Patients who had taken 0.99 g–2 g of MgO per day for more than 10 days during the 14 days before the start of treatment in the patient diary of the previous observation period.	10. Patients currently suffering from constipation due to organic diseases.
4. Patients who did not excrete “soft (muddy) or watery stools (BSFS type 6 or 7)” during the 14 days prior to the start of treatment and on the day of the start of treatment in the patient diary of the observation period and in the interview on the day of the start of treatment. Patients with diarrhea on the same day (each administration day) and the next day (the day after the end of the administration day) of the use of rescue medication (sennosides, bisacodyl, and sodium picosulfate) by rescue medication criteria will be excluded.	11. Patients currently suffering from active peptic ulcer.
5. Patients who excreted smooth and soft sausage-like stools (BSFS 4) at a frequency of less than twice a week for 14 days prior to the start of treatment in the patient diary of the observation period. This excludes the day on which the rescue medications (sennosides, bisacodyl, and sodium picosulfate) were used by rescue medication criteria (the day of each dose) and the day after (the day after the end of dose).	12. Patients with severe depressive or anxiety symptoms that are judged to affect the assessment of drug efficacy.
6. Patients who have not used or performed any rescue medication, concomitantly prohibited drug, therapy, or prohibited test since enrollment. Subjects who meet the criteria for rescue medication and have used the rescue medication (sennosides, bisacodyl, sodium picosulfate) less than or equal to two consecutive times will not be excluded.	13. Patients with a history of drug or alcohol abuse or current abuse within one year prior to obtaining consent.
7. Patients who did not use the rescue medication from the day before the start of treatment to the start of treatment.	14. Patients who have used or are planning to use the following prohibited drugs: Lubiprostone, elobixibat, polyethylene glycol (Macrogol 4000), and lactulose
8. Patients for whom the investigator or sub-investigator has not judged that it is inappropriate to start administration.	15. Patients who have been prescribed or will be prescribed antiparkinsonian, antipsychotic, antimanic, or psychostimulant medication at the time of enrollment.
	16. Patients who have undergone or are scheduled to undergo gastrointestinal endoscopy within 3 days prior to enrollment.
	17. Patients who have had or currently have a malignant tumor of the digestive system (excluding gastrointestinal cancers that have been cured by endoscopic treatment).
	18. Patients currently suffering from serious cardiovascular, respiratory, renal, hepatic, gastrointestinal, hematological, neurological or psychiatric diseases.
	19. Patients with a history of drug allergy.
	20. Patients who have participated or are currently participating in clinical trials, post-marketing clinical trials, or clinical research for other ethical drugs or medical devices within 12 weeks prior to obtaining consent.
	21. Patients who are judged inappropriate to participate in this study.

### Study flow

2.6

The flow of the study is shown in Fig. 1. The principal investigator or sub-investigator will check the eligibility criteria at visit 1 and medication initiation criteria at visit 2 (Table 1). During the observation period, patients will ingest a prescribed dose of 0.99 g–2 g of MgO. Patients who meet the medication initiation criteria will be asked to complete the blood tests and questionnaires provided in Table 2. During the medication period, MgO will be discontinued and linaclotide will be administered at a dose of 0.5 mg per day, which will be reduced or withdrawn depending on the symptoms of defecation. If there is no defecation while taking the study medication, the use of rescue medication will be acceptable according to the following protocol: the study medication is prescribed for each visit, and any remaining medication is collected by the physician in charge. The duration of medication will be 12 weeks.

**Fig. 1 fig1:**
[figure not shown]
Study flow.

**Table 2 tbl2:**
[figure not shown]
Schedule of the study..

#### Use of rescue medication

2.6.1

If there is “no defecation” for more than 3 days during the study period, the subject can take one type of medication according to the dosage and administration as directed by the principal investigator or sub-investigator. If there is no or insufficient defecation the following day, the subject can take another dose of rescue medication. If the second dose of rescue medication does not produce a bowel movement or is insufficient, the subject can use a rescue medication or enema according to the dosage and administration. The use of rescue medications or enemas will be documented in the patient's diary. The rescue medications include sennosides, bisacodyl, and sodium picosulfate. However, if the drug is used without meeting the criteria for rescue medication, it will be considered a prohibited medication.

#### Concomitant prohibited treatments

2.6.2

During the study period, the use of the drugs, treatments, and tests listed in Table 3 is prohibited.

**Table 3 tbl3:** Concomitant medications, treatments, or tests that are prohibited during the study.

**Drugs prohibited in combination with**

【**Ethical pharmaceuticals**】
1. Sennosides, bisacodyl, sodium picosulfate (when used within 3 days of non-defecation during the study period, and excluded when used under the rescue medication criteria)
2. Lubiprostone, elobixibat, polyethylene glycol (Macrogol 4000), lactulose
3. Anticholinergic drugs
4. Rhubarb
5. Antidiarrheals
6. Laxatives other than 1. and 2. (except for MgO in the observation period and on the first day of treatment period)
7. Narcotic analgesics, narcotics, and narcotic antitussives (narcotic antitussives are allowed on an ad hoc basis)
8. Antiparkinsonian drug
9. Antipsychotic drug
10. Antimanic drug
11. Psychostimulant

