#### Efficacy endpoints

2.10.1

The primary endpoint is the change from baseline in terms of the JPAC-QOL total score after 12 weeks of treatment. The secondary endpoints are listed in Table 4.

**Table 4 tbl4:** Study endpoints.

Study endpoints	
**Primary endpoint**	**Secondary endpoints**
Change in JPAC-QOL score from baseline at 12 weeks of linaclotide treatment	1. Change in weekly average of SBM frequency
	2. Percentage of subjects with SBM within 24 h of first dose
	3. Time to first SBM
	4. Change in weekly average of CSBM frequency
	5. Percentage of subjects with CSBM within 24 h of first dose
	6. Change in weekly average of stool forms
	7. Average weekly change in abdominal bloating severity score
	8. Average weekly change in abdominal pain and abdominal discomfort severity score
	9. Average weekly change in severity score of straining
	10. Change in JPAC-QOL overall score and subscale scores
	11. SF-12v2 summary score, change in subscale
	12. Satisfaction score on defecation

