### Statistical analysis

2.12

Efficacy analyses will be performed using FAS. The results of the statistical tests will be interpreted according to the FAS; PPS will be used to assess the robustness of the results based on the FAS. The primary endpoint is the change in the JPAC-QOL total score from baseline at week 12. A paired *t*-test will be performed at a two-sided significance level of 5% for the change in the JPAC-QOL total score between the baseline and week 12. Additionally, the point estimation and 95% confidence intervals for the mean change will be calculated.

As secondary analyses, subgroup analyses will be performed for the following factors:(1)Abdominal symptoms (with or without abdominal symptoms)(2)Gender (male, female)(3)Age (<65 years, ≥65 years)

The secondary endpoints are presented in Table 4. Summary statistics of the measured values and changes from baseline will be calculated for each time point for items 1, 4, and 6–11. Paired t-tests will be performed on the amount of change, and 95% confidence intervals for differences will be calculated. For items 2 and 5, the number and percentages of subjects as well as the 95% confidence interval will be calculated. For item 3, a Kaplan-Meier curve will be plotted, and the median and 95% confidence interval of the time to event will be calculated. The earliest discontinuation, failure to observe, and expiration during the observation period will be defined as censoring. For item 12, the number and percentages of patients in each category will be calculated at each time point.

For safety analysis, the number of cases and percentages of adverse events and adverse events that cannot be denied as related to the study drug will be calculated. For the measurable parameters in the clinical laboratory tests, summary statistics of the actual measured values and changes from baseline will be calculated for each time point using descriptive statistics. For countable parameters, a frequency tally will be performed at each assessment time point. A shift table of the laboratory measurement abnormalities observed at each time point from the baseline compared to the normal range during the treatment period will be recorded.

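### Section 2.6 and Table 3 disagree on MgO on the first treatment day, and the first-dose endpoints have no run-in reference to show the MgO background

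*Protocol article*

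**What the plan says.** On MgO during treatment, section 2.6 of the protocol article states: "During the medication period, MgO will be discontinued and linaclotide will be administered at a dose of 0.5 mg per day". It gives no exception. Table 3, item 6, lists as prohibited "Laxatives other than 1. and 2. (except for MgO in the observation period and on the first day of treatment period"), which takes MgO out of the ban for one day that belongs to the treatment period.

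Three secondary endpoints in Table 4 look at the time just after the switch:

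- item 2: "Percentage of subjects with SBM within 24 h of first dose"
- item 3: "Time to first SBM" (no start point is given)
- item 5: "Percentage of subjects with CSBM within 24 h of first dose"

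Section 2.12 fixes their analysis. "For items 2 and 5, the number and percentages of subjects as well as the 95% confidence interval will be calculated". Item 3 gets a Kaplan-Meier curve with a median and 95% CI, and on censoring the text says: "The earliest discontinuation, failure to observe, and expiration during the observation period will be defined as censoring". MgO intake is not mentioned. Items 1, 4 and 6–11, in contrast, are analysed as changes from baseline with paired t-tests and 95% CIs.

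**The concern.** There are two linked problems.

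The first is the text. A site that follows section 2.6 and a site that follows Table 3 could handle MgO differently on the day treatment starts.

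The second is interpretation. Every patient comes to treatment on MgO: medication initiation criterion 3 in Table 1 requires 0.99–2 g/day on more than 10 of the preceding 14 days, and no washout is described. A movement in the first 24 h may therefore be one that MgO would have produced anyway, whether from a dose taken that day or from the days before. With no control group, the patient's own run-in is the only internal reference, and the three endpoints closest to the switch are the ones that do not use it. What is at stake is any statement about how quickly linaclotide acts in patients who switch.

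**Working it through.** **1. The passages side by side.**

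| Place | MgO on the first day of the treatment period |
|---|---|
| Section 2.6 | Stopped; no exception |
| Table 3, item 6 | Exempt from the laxative ban |
| Section 2.12, items 2, 3 and 5 | Not addressed |

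Table 3 names the treatment period separately from the observation period, so the exemption is not just a restatement of run-in use.

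**2. Which endpoints are exposed.** Items 2 and 5 have a 24-h window that opens at the first dose. Item 3 has no stated start point. Read as a measure of onset, only its earliest events fall in the exposed time.

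**3. Is there a plan figure to reproduce?** Not for this point. The article gives no run-in SBM rate, no expected 24-h response and no share of patients taking MgO on day 1. The sample size rests on the week-12 JPAC-QOL change and is a separate matter. It does reproduce: with d = 0.46/0.68, the paired t-test has power 0.887 at n = 24 and 0.9005 at n = 25; 25/0.8 = 31.25, rounded up to 32; 2 × 32 = 64.

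**4. Background, on assumed rates.** Let λ be the run-in SBM rate per week, and assume random (Poisson) timing. The chance of at least one SBM in any 24 h is 1 − exp(−λ/7).

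| Assumed λ per week | 1 − exp(−λ/7) |
|---|---|
| 2 | 0.249 |
| 3 | 0.349 |
| 4 | 0.435 |
| 5 | 0.510 |

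The initiation criteria in Table 1 limit BSFS 4 stools and exclude BSFS 6–7 stools, but they set no upper limit on how often patients have a bowel movement, so they do not rule out these rates. The table concerns SBM only and does not carry over to CSBM.

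**5. The day-1 MgO part, also on assumptions.** If a share m of patients take MgO on day 1, and it raises their 24-h SBM rate from p0 to p1, the reported rate is too high by m × (p1 − p0). With p0 = 40% and p1 = 50–60%:

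- m = 25%: 2.5 to 5 points
- m = 100%: 10 to 20 points

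For comparison, the 95% CI half-width at n = 64 and 40% is 1.96 × √(0.4 × 0.6/64) = 0.12, or 12 points. That interval covers sampling error only, and neither the background in step 4 nor this shift.

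**The case against.** The strongest reply is that the two passages need not conflict. Section 2.6 can be the general rule and Table 3 a specific exception for the transition day, perhaps only so that MgO taken before the start visit does not count as a prohibited drug. Criterion 5 of the per-protocol set (section 2.11) counts administration from the start of treatment or the day after, so the first linaclotide dose may come after the exempted day. This is plausible, but the article does not say it, and MgO from the day before could still act within 24 h of a first dose.

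The article also does not define SBM. Whether a movement after laxative intake counts may be settled in the full protocol.

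The protocol does take care over other laxatives just before the start: criterion 7 in Table 1 requires "Patients who did not use the rescue medication from the day before the start of treatment to the start of treatment". It gives no reason for this rule, so the contrast with MgO is suggestive but does not prove that carry-over was recognised.

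Finally, these are three of twelve secondary endpoints in an exploratory study. They are analysed without a test, and items 1 and 4 already compare weekly SBM and CSBM frequency with baseline. That limits the consequence. It does not supply a reference for early response, because a weekly average does not describe the first 24 h.

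**Conclusion.** The point holds in a limited form. The two statements on MgO must be reconciled. As planned, items 2 and 5, and the earliest events of item 3, cannot be separated from the MgO background.

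A reader might infer more: that all three endpoints measure MgO plus linaclotide, or that a hypothetical 24-h response of 60% would be 41–85% MgO effect (0.249/0.60 to 0.510/0.60). The documents support neither. Table 3 permits MgO on day 1 but does not require it, the first dose may fall a day later, and item 3 has no stated start point. The percentages rest on assumed SBM rates, random timing and an assumed response. They would be the same if Table 3 banned MgO on day 1, because they describe the background facing any 24-h proportion without a control.

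The size of the bias therefore cannot be derived from the article. The 25–51% range shows only that the background need not be small. The week-12 primary endpoint and the sample size are unaffected.

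**What to change.** 1. Reconcile section 2.6 with Table 3, item 6, so that one rule covers MgO on the first treatment day. No view is taken on which rule is right. Make sure any intake that day is recorded, if the diary does not already do so.
2. For items 2 and 5, compute the same 24-h proportion from the run-in diary, for example over the last run-in days free of rescue use. For each patient, take the first-dose result (0 or 1) minus the proportion of run-in windows with an event. Report the mean difference with its 95% CI beside the planned percentage.
3. For item 3, state the start point. If the diary timing allows, show a run-in curve of time to next SBM, from a fixed run-in day, beside the treatment curve.
4. If MgO on day 1 remains allowed, describe these endpoints as first-dose response with MgO possibly on board.

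Steps 2 to 4 matter even if the exemption goes, since patients would still arrive directly from daily MgO. The comparison remains before-and-after and does not replace a control group.

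The cost is one reconciled sentence and a small additional analysis of diary data that the run-in already collects. The downside is that early response will probably look less favourable.
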